
### Target Population

Women of reproductive age, family members, health service cadres, health management committee members, and communities. We estimate conservatively that there will be over 4000 pregnancies per year in the study area.

### Sample size

The study will include all pregnancies in all 43 VDCS. We estimate that each VDC will yield about 100 births per year and that the proportion of birth attendance by trained health workers is currently 20%. We estimated sample size using the equations of Hayes and Bennett [57], assuming two treatment groups and unmatched clusters of approximately equal size. We set a value of *k *- the between-cluster coefficient of variation - equal in intervention and control groups, and added 2 to the estimated cluster number to account for loss of degrees of freedom as a result of stratification. All estimates are based on a two-tailed 5% significance level. The value of *k *is likely to be 0.3 on the basis of estimates of neonatal mortality rate from the Makwanpur study. However, we have estimated sample size with a range of *k *from 0.25 to 0.35.

For two years of intervention (200 births per cluster), if *k *= 0.35, 42 clusters would detect an increase in trained attendance from 20% to 30% at 90% power, and from 20% to 28% at 80% power. If *k *= 0.30, 42 clusters would detect an increase in trained attendance from 20% to 28% at 90% power, and from 20% to 27% at 80% power. If *k *= 0.25, 42 clusters would detect an increase in trained attendance from 20% to 27% at 90% power, and from 20% to 26% at 80% power. Overall, a conservative level of powers, births and values of *k *suggests that the sample size will be able to detect an increase in birth attendance by trained health workers of around 10% over two years.

### The intervention

The intervention being implemented in 21 clusters has two components: community mobilisation through women's groups, and strengthening of health facility management committees. Previously, our intervention employed a cadre of local female facilitators to lead groups through a participatory action cycle about maternal and newborn health [8,11]. Although it was successful in reducing newborn mortality, most women in the study gave birth at home without a trained health worker in attendance [13]. Qualitative research found that there was often lack of trust in local health facilities and contact between women's groups and health institutions was limited [15]. In dialogue with the GoN Family Health Division, we sought to develop a model of community mobilisation that was scaleable within existing government health systems, was more focussed on enabling trained health worker attendance at deliveries, and could enable links to be developed between communities and health facilities. We have developed an intervention that fits national policy by engaging FCHVs to facilitate discussions on maternal and newborn health in their regular monthly women's group meetings. Our model of support and supervision is less intensive than in previous studies, with a lower ratio of FCHVs to supervisors, increasing the potential for scale-up within existing systems. We are also conducting HMC strengthening through an Appreciate Inquiry approach endorsed by the Family Health Division [40,58]. We aim to increase links between communities and health institutions and improve access to quality maternal and newborn health services.

#### Women's groups

195 FCHVs received four days training to orientate them about our previous research in Makwanpur, familiarise them with the participatory action oriented approach of the intervention and develop their facilitation and reporting skills. They received refresher training on their roles and responsibilities and were introduced to the manual they will use to help guide discussions. Formative data show that 50% of FCHVs in the intervention area had difficulty in reading and writing. The manual contains a simple discussion guide for each meeting, stating its objectives and encouraging the use of tools or games. FCHVs are supervised by seven MIRA field supervisors who co-ordinate monthly orientation meetings in each VDC to discuss progress, problems, and the next women's group meeting agenda. Supervisors also support FCHVs while they are conducting meetings, observing an average of four meetings per month. Supervisors meet with a Facilitation Manager once a month to report on progress and discuss issues from the field. 203 women's groups are led through a participatory action cycle. In the first seven meetings groups are encouraged to interact with their community in identifying barriers to trained health worker attendance at deliveries, and then to develop ways of addressing them. Groups then have a community meeting where they present and discuss the barriers and corresponding strategies to deal with problems, seeking support and commitment from community members. After the community meeting, groups develop plans and lead the implementation of strategies to address problems. This phase takes place without a discussion manual and has no set duration. After around four months, groups will be encouraged to evaluate the strategies they have implemented with the aid of a manual, and plan the next steps. We will complete two cycles of problem identification, planning, implementation and evaluation within the study period.

#### Health Management Committee strengthening

We developed the intervention after discussions with the Support for Safe Motherhood Programme, United Mission to Nepal, and Appreciative Inquiry practitioners in India and Nepal. The intervention uses the principles of the 'four D' cycle of discovery, dream, design and destiny [40]. We also visited HMCs that had engaged in appreciative planning and action in order to learn from their experience. We employed a consultant to conduct a training of trainers on the Appreciative Planning and Action process with MIRA researchers, representatives from the District Public Health Office, District Development Committee, and Family Planning Association of Nepal. Thereafter, we conducted four-day workshops in each of the 21 intervention VDCs over four months. Workshops were held in local health facilities and attended by a district level representative who had attended the training of trainers. A senior MIRA researcher facilitated each workshop. HMC members, community representatives, and health facility employees participated. Our formative research found 18 out of 43 HMCs scored well on indicators of resource mobilisation, staff management, service monitoring, management of health volunteers, and regularity of meetings. 10 were in control areas, and eight in intervention areas. We also found that many HMCs had not received an orientation about their roles and responsibilities, and we discussed this on the first day of the workshop. We familiarised participants with the maternal and newborn health situation in Nepal, government strategies and priorities, and our research. After briefing participants about the Appreciative Inquiry methodology and philosophy using stories, reports and proverbs, participants were invited to 'discover' the successes of their health institution and remember who provided support or resources to facilitate this success. Participants then 'dreamt' of how they would like their health institution to be and the quality of services they would like to provide for maternal and newborn health. In the next phase they 'designed' a strategy to achieve their vision, using resources and opportunities discussed in the discovery phase, detailing goals and strategies to reach them, and allocating responsibilities for activities. We will support and monitor the progress of the HMCs through follow-up meetings every two to three months. These discussions will encourage HMCs to track their progress on strategy implementation and add or change plans as necessary. The last phase of the appreciative planning and action approach, 'destiny', will be completed after HMCs have implemented their plans, and participants will present their accomplishments and what they have learned.

### Data collection

Data on the primary outcomes will be collected through a surveillance system for all births in the 43 VDCs. The system is similar to those implemented in other community based trials[14,17,59-61]. We incentivise nominated local women to identify births, newborn deaths and deaths of women between the ages of 12 and 49 years. They communicate vital event information at monthly meetings to a cadre of interviewers who verify the events and visit families to administer a questionnaire. Questionnaires to measure our primary and secondary outcomes are based on previous tools. We piloted 100 questionnaires and adapted the tool based on discussions with our experienced team of interviewers. Standard WHO verbal autopsy tools were translated from English to Nepali, back translated and field tested, and are used to ascertain cause of death [62].

### Project Timeline

Prospective baseline enrolment of births: 19^th ^November 2009 - 30^th ^September 2010.

Enrolment of births in the trial: 1^st ^October 2010 - 30^th ^September 2012.

Women's group meetings: March 2010 - 30^th ^September 2012.

Health management committee strengthening workshops: June 2010 - 30^th ^September 2012.

Health management committee strengthening follow-up: December 2010 - September 2012.

Intervention duration: 1^st ^October 2010 - 30^th ^September 2012.

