### Public engagement

We will promote public engagement in our research locally, nationally and internationally.

Locally, we have been engaged in dialogue with community representatives, political bodies, community-based organisations (CBOs) and NGOs since cluster allocation. Intervention areas will have formal community meetings between women's groups and community members after seven months and at least once more during the intervention period. MIRA employees will be present at these meetings. After completion of the study, we will disseminate the results formally at meetings for all VDCs of Makwanpur district. We will invite VDC representatives, health management committee members, health post in-charges, teachers, user group members, NGOs, CBOs, local intellectuals, political party representatives, cooperative members, VDC secretaries, club members and local residents. After presenting the findings, the forum will be open for discussion and comment and feedback will be taken. Likewise, we will disseminate the findings at district level. The District Health Officer, District Public Health Officer, Local Development Officer, Community Development Officer, Regional Administrator, Women's Development Officer, Municipality Chief and representatives of International NGOs and NGOs working in the women's and children's sectors will be invited to the meeting. We will engage in open discussion at these meetings.

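### The Project Timeline counts births to 30 September 2010 as baseline, although women's groups had been meeting since March and committee workshops since June 2010

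*Protocol article*

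**What the plan says.** All the dates stand in one short list, Project Timeline:

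- "Prospective baseline enrolment of births: 19^th ^November 2009 - 30^th ^September 2010"
- "Women's group meetings: March 2010", continuing to 30 September 2012
- "Health management committee strengthening workshops: June 2010 - 30^th ^September 2012"
- "Intervention duration: 1^st ^October 2010", continuing to 30 September 2012; trial births are enrolled over the same two years.

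The section The intervention names women's groups and committee strengthening as its two components in the 21 clusters. On the early group meetings, Women's groups says: "In the first seven meetings groups are encouraged to interact with their community in identifying barriers to trained health worker attendance at deliveries", and that groups then work out how to deal with those barriers. A community meeting follows, and then: "After the community meeting, groups develop plans and lead the implementation of strategies to address problems". Public engagement times that meeting: "Intervention areas will have formal community meetings between women's groups and community members after seven months". On workshops, Health Management Committee strengthening reports: "we conducted four-day workshops in each of the 21 intervention VDCs over four months".

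Analysis strategies plans a comparison of key variables between arms at baseline, a primary comparison on two years of births described as years of intervention, and optional ancillary analyses that may include an interrupted time series. The article nowhere describes a run-in or phase-in.

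**The concern.** A baseline is meant to describe the arms before the intervention could act. Here both components were under way in the intervention clusters during the period given that label, and the group meetings were already about the primary outcome. Pooling births from before and after the first meetings means that a difference between arms in attendance, place of delivery or care-seeking could be chance imbalance, early effect or both, and the table could not tell them apart. Characteristics that the intervention cannot change are not at risk.

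The label also blurs exposure. The outcome period is described as two years of intervention, yet on the printed dates groups meet for 30 to 31 months.

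**Working it through.** The plan gives no figure of its own to reproduce. The check is calendar arithmetic, followed by a sizing under stated assumptions.

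**Inputs.** Dates are from Project Timeline. About 100 births per cluster per year, 20% trained attendance and k = 0.30 are from Sample size. There are 21 intervention and 22 control clusters. Only months are printed for the start of activities, so first and last day of the month give the range.

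**Overlap**
- Labelled baseline, 19 November 2009 to 30 September 2010: 316 days.
- Groups from 1 March: 214 days inside it (214/316 = 68%), 102 before. From 31 March: 184 days (58%), 132 before.
- Workshops from 1 June: 122 days (39%). From 30 June: 93 days (29%).
- Groups to 30 September 2012: 945 days (31.0 months) or 915 days (30.1 months).

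**Expected intervention-arm births**, 2,100 × days/365
- Whole window: 1,818 (86.6 per cluster).
- After groups began: 1,231 or 1,059.
- Before groups began: 587 or 759 (27.9 or 36.2 per cluster).

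**Possible shift in the intervention-arm baseline.** Sample size powers for a proportion over 200 births per cluster, which is a two-year average. Let the effect grow linearly from the first meeting (an assumption) and average A points over the 731 trial days. With E exposed baseline days and slope s per day, A = s(E + 365.5), and the shift is (E/316) × sE/2. Hence

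shift = A × E² / [632 × (E + 365.5)]

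- E = 214: 0.125 × A, which is 1.00 points (A = 8) or 1.25 (A = 10).
- E = 184: 0.0975 × A, which is 0.78 or 0.97.
- No effect before October 2010: 0.

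**Precision of the baseline arm difference**, with m births per cluster and stratification ignored:

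SE = √{[0.20 × 0.80/m + (0.30 × 0.20)²] × (1/21 + 1/22)}

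- Whole window, m = 86.6: 2.25 points.
- Before groups only, m = 27.9 or 36.2: 2.95 or 2.73 points.
- March-September only, m = 58.6 or 50.4: 2.43 or 2.51 points.

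**Trade-off.** The short window alone is more accurate only if the bias exceeds √(SE_short² − SE_full²), which is 1.90 points for a 1 March start and 1.55 for 31 March. At the largest sized shift, 1.25 points with a 1 March start, root mean square error is √(2.25² + 1.25²) ≈ 2.58 for the whole window against 2.95 for the short one. Replacing the whole window by the short one is therefore not justified on accuracy; showing both is.

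**The case against.** The strongest reply is that the dates fit a coherent preparatory phase. Groups meet monthly, so seven meetings from March 2010 end about September, with the community meeting and strategy implementation after that. Four months of workshops from June end between late September and late October 2010, and committee follow-up starts in December. Both components would reach implementation around 1 October 2010. The Background also reports that impact in the similar Indian trial grew over time. All of this stands, and it makes a large early effect unlikely. It does not rescue the label: the article calls these births baseline, dates the intervention from October and describes no run-in.

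It is also fair that the start months are printed openly, that the key variables for the baseline comparison are not listed, and that detail of the baseline table may sit in an analysis plan not shown. The point therefore rests on the wrong label and dates, not on an absent table specification.

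A reader might go further in four ways that the document does not support.

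- *The primary result is contaminated.* It uses births from October 2010 to September 2012 and adjusts for socioeconomic status and religion, not for baseline outcome.
- *The interrupted time series will be biased.* With a break at 1 October 2010 and linear growth from the first meeting, the share of the slope change absorbed into the pre-period would be 3u² − 2u³ with u = E/316, or 62-75%. But that analysis is optional and no break is fixed.
- *The monitoring committee will be misled.* Interim analysis does not say which births it will use to judge comparability.
- *Births before March 2010 are free of any women's group influence.* Earlier programmes ran to 2008 in two strata, and most of the groups they mobilised were still meeting a year after support ended. Stratified allocation should balance this between arms.

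**Conclusion.** The Project Timeline contradicts itself. On its own dates, 58-68% of the labelled baseline follows the start of intervention activity in the intervention arm. That needs no assumption beyond the day of the month.

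The consequence is bounded. It touches the baseline comparison of variables that the intervention targets, and the stated length of the intervention. The shift is zero if nothing changes before October 2010 and about 0.8 to 1.25 points under linear build-up to an average effect of 8 to 10 points, roughly a third to just over half of the 2.25-point standard error. Linear growth from the first meeting is an assumption, and a generous one given the order of activities. If 8 to 10 points were reached only at the end of September 2012, the shift would be smaller: 10 × (214/316) × 0.5 × (214/945) = 0.77 at most.

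The inconsistency should be corrected, but it does not threaten the main result.

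**What to change.** - State in Project Timeline that intervention activities began in March 2010 and that 1 October 2010 starts the counting of outcomes. Label March-September 2010 a run-in.
- In the baseline comparison, show outcome and care-seeking variables separately for births before the first group meeting and for run-in births. Keep the whole window for variables that the intervention cannot change.
- If an interrupted time series is done, do not treat March-September 2010 as pre-intervention.
- Leave the primary comparison as planned, described as two years of outcomes after a run-in of about seven months.
- As a minor editorial matter, reconcile the printed workshop end date of 30 September 2012 with the four months reported in Health Management Committee strengthening. The later closing phase of the committee process may explain it, but the article does not say so.

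There is no extra fieldwork: given dates of delivery, the split is a filter plus extra table columns. The cost is precision. The earlier period has about 28 to 36 births per cluster instead of 87, and a standard error of about 2.7 to 3.0 points instead of 2.25, which is why the run-in births should be shown beside it and not dropped.

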### Data management

Questionnaire responses will be checked in the clusters by field coordinators, and re-checked by a data auditor before data entry in the district office in Hetauda. At least 10% of interviews will be observed. Information will be entered in a relational database management system (RDBMS) in Microsoft SQL Server 2007, through an interface programmed in Visual Basic for Applications. The system will incorporate validation constraints. Hard copies of records will be stored in a filing system in a lockable room. Electronic output will be anonymised.

We are also conducting a concurrent process evaluation to describe the context of the intervention, how it is being implemented and who is participating, and collecting information to develop hypotheses about how the intervention may be effective. The integration of process evaluations with randomised controlled trials enables the external validity of the trial findings to be assessed, [63] and may help in successful replication [64]. Process data also help understand and explain trial results [65]. Qualitative and quantitative data are being collected, entered and analysed by our process evaluation team who have received training and support in qualitative and quantitative techniques.

#### Interim analysis

We will convene a Data Monitoring Committee in 2012 after 18 months of project activities. The board will include national and international expertise in the conduct of randomised controlled trials and will review data and procedures according to the DAMOCLES guidelines [66]. The committee will be decide whether the study protocol has been followed adequately, whether enrolment has been adequate, and whether randomization has resulted in comparable groups so that, in the absence of interventions, it would be reasonable to expect similar health outcomes over time. It will review interim data for completeness, quality and adherence to ethical requirements, and will make recommendations on the continuation of the trial or its modification.

#### Analysis strategies

Data will be checked for consistency and completeness in both the RDBMS and after export to Stata. An analysis plan will be developed in accordance with the CONSORT reporting guidelines [67]. We will present a trial profile and a comparison of key variables between intervention and control arms at baseline. Details of the number of clusters and individuals included in the analysis will be provided, and the analysis will be intention-to-treat. We will compare the primary outcome in intervention and control arms, using data for two years of intervention. We will conduct the analysis at the level of the individual, and the procedure of choice will be random effects logistic regression models grouped on cluster. If quadrature checks suggest that this is inappropriate, we will use generalised estimating equations. Analyses will be adjusted for socioeconomic status and religion. The findings will be augmented by ancillary analyses, which may include dose-response, interrupted time series and process evaluations.

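### The primary model leaves out each cluster's pre-intervention level of the outcome; adding it would give a modest to moderate gain in precision

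*Protocol article*

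**What the plan says.** The Analysis strategies section fixes the comparison: "We will compare the primary outcome in intervention and control arms, using data for two years of intervention". The model is an individual-level random effects logistic regression grouped on cluster, with generalised estimating equations as fallback. Two adjustment variables are named, socioeconomic status and religion. Baseline data enter through a table comparing the arms, and possibly through an ancillary interrupted time series. The same section says that an analysis plan is still to be written.

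The Project Timeline lists "Prospective baseline enrolment of births" from 19 November 2009 to 30 September 2010. The Data collection section states: "Data on the primary outcomes will be collected through a surveillance system for all births in the 43 VDCs". The timeline also starts women's group meetings in March 2010 and committee workshops in June 2010, both inside the baseline window, although it dates the intervention period from 1 October 2010.

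**The concern.** A cluster's earlier level of an outcome is usually among the better predictors of its later level. Here most of the variance of a cluster's attendance proportion lies between clusters, so a cluster-level baseline covariate acts on the component that limits power. The Design section itself says that earlier project work had left measurable differences between clusters.

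The power calculation also rests on a borrowed k, which "is likely to be 0.3 on the basis of estimates of neonatal mortality rate from the Makwanpur study", not on attendance. If attendance varies more between clusters than mortality does, the trial has less power than stated. Baseline adjustment recovers some of that loss and corrects for chance imbalance between arms in prior attendance.

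**Working it through.** **Inputs from the Sample size section.** "All estimates are based on a two-tailed 5% significance level". The Hayes and Bennett formula is used, "assuming two treatment groups and unmatched clusters of approximately equal size", and the authors "added 2 to the estimated cluster number to account for loss of degrees of freedom as a result of stratification". They estimate that "each VDC will yield about 100 births per year and that the proportion of birth attendance by trained health workers is currently 20" per cent. So p0 = 0.20, m = 200 births per cluster over two years, and k = 0.30 (range 0.25 to 0.35).

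**Input not in the document.** The correlation rho between a cluster's true attendance rates in the two periods. I show 0.3, 0.5 and 0.8.

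**1. The plan's own figure.** Clusters per arm = 2 + (z₁ + z₂)² [p0(1−p0)/m + p1(1−p1)/m + k²(p0² + p1²)] / (p1 − p0)². For k = 0.35, 20% to 30%, 90% power:
- bracket = 0.00080 + 0.00105 + 0.1225 × 0.13 = 0.017775
- 2 + 10.508 × 0.017775 / 0.01 = 20.68, so 21 per arm and 42 in all, as stated.

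With 21 per arm, the detectable rates in the other five scenarios are 28.3, 28.4, 27.0, 27.0 and 25.9%. Rounded, these match the stated 28, 28, 27, 27 and 26%.

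**2. Share of variance between clusters.** At k = 0.30, k²p² = 0.09 × 0.04 = 0.0036 and p(1−p)/200 = 0.0008. The share is 0.0036/0.0044 = 82% (76% at k = 0.25, 86% at k = 0.35).

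**3. Usable baseline.** The window is 316 days. Taking 1 March 2010 as the start of the groups, 102 days precede it and 214 (68%) do not. Births per cluster: 100 × 102/365 ≈ 28. The reliability of a 28-birth proportion at k = 0.30 is 0.0036/(0.0036 + 0.16/28) = 0.39 (0.46 at k = 0.35).

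**4. Variance removed.** r = rho·k²p² / √[(k²p² + p(1−p)/28)(k²p² + p(1−p)/200)], and the fraction removed is r². Example, k = 0.30 and rho = 0.5: r = 0.0018/√(0.00931 × 0.0044) = 0.281, r² = 0.079.

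**5. Power for 20% against 28%.** At k = 0.30 the unadjusted bracket is 0.0008 + 0.001008 + 0.09 × 0.1184 = 0.012464. With 19 effective clusters per arm (21 less the 2 added), SE = √(0.012464/19) = 0.0256, and 0.08/0.0256 − 1.96 = 1.16 gives 87.8%. With 21 it is 90.7%. For adjusted power the variance is multiplied by 1 − r².

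| k | rho | variance cut | SE ratio | power without (19–21 clusters) | power with |
|---|---|---|---|---|---|
| 0.30 | 0.3 | 3% | 0.99 | 88–91% | 89–92% |
| 0.30 | 0.5 | 8% | 0.96 | 88–91% | 90–93% |
| 0.30 | 0.8 | 20% | 0.89 | 88–91% | 94–96% |
| 0.35 | 0.3 | 4% | 0.98 | 78–82% | 79–83% |
| 0.35 | 0.5 | 10% | 0.95 | 78–82% | 82–86% |
| 0.35 | 0.8 | 25% | 0.86 | 78–82% | 89–91% |

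This is a linear approximation on the risk-difference scale, before any overlap with other covariates.

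**6. Why not the whole window.** With about 87 births per cluster (100 × 316/365), reliability at k = 0.30 is 0.66, so the regression slope is about 0.66 × rho. Suppose births on or after 1 March 2010 carry 25–50% of the full effect (an assumption). The intervention arm's baseline then contains 0.68 × 0.25 to 0.68 × 0.50, or 17–34%, of that effect. Adjustment would shrink the estimate by 0.33 × 17–34% = 6–11% at rho 0.5, and by 0.53 × 17–34% = 9–18% at rho 0.8. The SE falls by 7% and 19% respectively, so much or all of the gain could be lost and the estimate biased towards no effect.

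**7. Form of the covariate.** A raw log odds is undefined for a cluster with no attended birth. With beta-distributed cluster rates, k = 0.35 and 28 births, the chance per cluster is 1.23% at 20% attendance. Over 43 clusters, 1 − 0.9877⁴³ = 41%. At 17%, the rural level given under Setting and formative work, it is 59%.

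**The case against.** The strongest reply is that this is an option not taken. The comparison is randomised and valid without the covariate, the sample-size figures reproduce, and at k = 0.30 power for 20% against 28% is already 88–91%. An analysis plan is promised and could add the term. All of that stands, and it limits the point to a recommendation. It does not remove it, because the protocol does not leave the covariates open: it names two, and this one is not among them.

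A reader might infer that the plan gives up a large gain at no cost. The documents do not support that. The correlation between periods is not given, and there are reasons to doubt a high one: attendance rose from about 5% in 2000 to 17%, free delivery care went national in 2009, and the strata had different earlier programmes running to 2008. The clean baseline is short and the covariate noisy. Strata, socioeconomic status and religion would explain some of the same variance. That every cluster has baseline data from November 2009 is a reasonable inference from the surveillance description, but the timeline does not say so.

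**Conclusion.** The point holds as an efficiency improvement. The stated adjustment set omits a predictor that the trial appears to collect anyway. At k = 0.30 it would reduce the variance by about 3% to 20% over rho 0.3 to 0.8, and at k = 0.35 by about 4% to 25%. These figures assume evenly spread births, 20% attendance at baseline, a group start on 1 March 2010 and no overlap with other covariates; overlap would make the gain smaller.

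It would be wrong to conclude that the primary analysis is biased or invalid without the term, or that the full baseline period could safely be used: intervention activity had begun in two-thirds of it.

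**What to change.** In the analysis plan, before any comparison of outcomes by arm, add one cluster-level covariate to the primary model: the proportion of births attended by trained health workers among births before the first women's group meeting in March 2010. A shrunken or continuity-corrected log odds would also serve. Do the same for institutional delivery with its own baseline level. State that later baseline births are not used in the covariate, reconcile the baseline and intervention dates in the Project Timeline, and confirm that surveillance was running in all 43 clusters from November 2009.

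The cost is a sentence or two and one degree of freedom, with no new data. If the correlation between periods proves low, the gain is small and little is lost.
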